APPENDIX 16. UMSP ADVERSE EVENT RECORD FORM..…………………………………………..59

**1.0. Summary**

| **Title** | Combination therapies for treatment of uncomplicated malaria in Uganda: evaluation of efficacy, safety, and tolerability |
| --- | --- |
| **Description** | Randomised, single-blinded trials comparing combination antimalarial regimens for treatment of uncomplicated falciparum malaria with 28-day follow-up. |
| **Participants** | Ugandans age > 6 months. |
| **Clinical Sites** | The studies will be conducted at the seven Uganda Malaria Surveillance Project (UMSP) sentinel sites. The Ugandan Ministry of Health (MoH) originally established these sites in 1998 in collaboration with the East African Network for Monitoring Antimalarial Treatment (EANMAT). |
| **Selection Criteria** | 1. Age > 6 months. 2. Fever (> 37.5ºC axillary) or history of fever in the previous 24 hours. 3. Absence of any history of serious side effects to study medications, including allergy to sulfa drugs 4. No evidence of severe malaria or danger signs 5. No evidence of a concomitant febrile illness 6. *P. falciparum* mono-infection 7. Parasite density > 2000/ul and < 200,000/ul 8. Agreement to return for all scheduled follow-up visits 9. Provision of informed consent 10. No history of anti-folate or amodiaquine use in past 7 days 11. Absence of pregnancy |
| **Follow-up** | Subjects will be asked to return on Days 1, 2, 3, 7, 14, 21, 28, and any unscheduled day that they feel ill for follow-up assessment. |
| **Study objectives** | To assess the efficacy, safety and tolerability of alternative antimalarial therapies for treatment of uncomplicated falciparum malaria as they compare to chloroquine/sulfadoxine-pyrimethamine (CQ/SP) treatment. |

### 2.0 INTRODUCTION

### 2.1 Background

Malaria remains one of the most serious global health problems and a leading cause of morbidity and mortality in Uganda. Appropriate case management, focusing on prompt treatment with effective antimalarial drugs, is the foundation of malaria control throughout sub-Saharan Africa. For decades, chloroquine (CQ) was the mainstay of antimalarial therapy, but the emergence of *P. falciparum* resistance to CQ has challenged control efforts.1 The spread of CQ resistance has been temporally associated with increased malaria-related morbidity and mortality in Africa, highlighting the urgent need to change antimalarial treatment policy in the face of rising CQ resistance.2 Unfortunately, the optimal alternative to CQ is not clear and available drugs are limited by cost, efficacy, and safety concerns. In 2000, the Ugandan MoH re-evaluated the national antimalarial drug policy in response to expanding CQ resistance. The combination of CQ plus sulfadoxine-pyrimethamine (SP) was chosen to provisionally replace CQ as first-line treatment for uncomplicated malaria. However, at the time that this decision was made, the efficacy and safety of the CQ/SP combination had not been evaluated in Uganda and it is anticipated that pre-existing resistance to both agents will limit the effective lifespan of this combination. To facilitate rational drug policy decision-making in the future, the investigation of alternative antimalarial regimens must continue. Regimens currently under consideration in Uganda for treatment of uncomplicated malaria include amodiaquine (AQ) plus SP, artesunate (AS) plus SP, and AS + AQ. Other possible therapies include artemether-lumefantrine (Co-Artem), and chlorproguanil/dapsone (Lapdap) combinations, when this agent is available.

Malaria control in East Africa is approaching a crisis. Use of CQ to treat malaria has failed on a public health level. SP resistance is already increasing and is likely to spread rapidly. Combination treatment with currently available monotherapies appears to be the most promising hope for treatment of malaria in the region. The lack of therapeutic options and need to confront rising CQ resistance and resultant increase in malaria-associated morbidity and mortality is forcing East African countries, including Uganda, to consider the introduction of combination antimalarial therapies on a large scale. In the absence of adequate data on the tolerability and efficacy of these regimens, the need for additional data on combination antimalarial therapy cannot be overstated.

### 2.2 Rationale

We are proposing to conduct drug efficacy studies to evaluate the efficacy and safety of combination antimalarial regimens for treatment of uncomplicated falciparum malaria in Ugandans. The choice of combination regimens to be tested in these studies will be driven by alternative antimalarial regimens prioritised by the Ugandan MoH and EANMAT. Generally, CQ + SP will serve as the standard treatment and will be compared to one or more alternative regimens including AQ/SP and AQ/AS. The data that is collected in these studies will be made directly available to the Ugandan MoH to assist in drug policy decision-making.

### 3.0 STUDY AIMS

To assess the efficacy, safety, and tolerability of alternative combination antimalarial therapies as they compare to the standard CQ/SP treatment.

### 4.0 STUDY DESIGN

### 4.1 Overall Design

These studies shall be randomised, single-blinded trials designed according to World Health Organization (WHO) guidelines for assessment of therapeutic efficacy of antimalarial agents in areas of intense transmission3 with slight modifications. The target population is residents of the catchment areas of the sentinel health centres. The available population is residents aged 6 months and above who have symptoms suggestive of malaria and a positive screening thick blood smear and who are referred to the clinics for screening. Subjects who meet the inclusion criteria and are enrolled in the trial will be randomised to treatment with one of the combination regimens and will be followed for 28 days. Repeat evaluations will be performed on days 1, 2, 3, 7, 14, 21, and 28 and will include assessment for the occurrence of any possible adverse event. Treatment efficacy outcomes will be assessed using modifications of WHO clinical and parasitological classification criteria (Appendix 3).

### Study outcome and measurement

### 4.2.1 Primary outcome

Response to treatment will be classified according to WHO criteria (Appendix 3), using clinical (1996: ACR, ETF, LTF) and parasitological (S, RI/RII/RIII) classification systems, with slight modifications.1 In addition, patient outcomes will be classified using the newly proposed WHO classification system (2002: ACPR, ETF, LCF, LPF), for purposes of data reporting.2 The efficacy of the combination regimens will be assessed by comparing the proportion of patients with clinical treatment failure at 28 days. Clinical outcome will be dichotomised into success (ACR) and failure (ETF or LTF). Pair wise comparisons between regimens will be made on an intention-to-treat basis.

### 4.2.2 Secondary outcome

The efficacy of the combination regimens will also be assessed by comparing the treatment groups as follows:

1. Proportion of patients with clinical failure (ETF/LTF) at 14 days of follow-up (Appendix 3)
2. Proportion of patients with parasitological resistance (RI/RII/RIII) at 14 and 28 days of follow-up (Appendix 3) to supplement results of clinical outcome and to facilitate comparison with historical data.
3. Proportion of patients with treatment failure according to new WHO guidelines (ETF/LCF/LPF) at 14 and 28 days of follow-up (Appendix 3).
4. Rate of fever clearance: presence or absence of objective fever (axillary temperature > 37.5C) or patient report of fever on days 1, 2, 3
5. Rate of parasite clearance: proportion of positive vs. negative thick blood smears on day 2 and day 3
6. Change in mean haemoglobin from day 0 to 28
7. Proportion gametocytemic: presence vs. absence of gametocytes on any follow-up thick blood smear; proportion gametocytemic on days 2, 3, 7, 14, 21, and 28.

The safety and tolerability of the combination regimens will be further compared as follows:

1. Incidence of serious adverse events (AEs): proportion of patients experiencing any serious AE in each treatment group during the 28-day follow-up period.
2. Incidence of AEs: proportion of patients experiencing any mild/moderate/severe/life-threatening AEs during the 28-day follow-up period
3. Incidence of AEs by specific sign or symptom during the 28-day follow-up period

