### 5.2. Selection criteria:

Patients shall be assessed for the inclusion criteria at the time they are referred to the study clinic with a screening thick blood smear parasitaemia of > 2000/ul and < 200,000/ul. If the following criteria are met, patients will be enrolled in the study, assigned a study number, have blood removed by finger-prick for further laboratory tests (Giemsa-stained thick and thin blood smears, Hb measurement and blood collected on filter paper) and will be treated promptly according to their assigned antimalarial study regimen.

1. Age 6 months and above.
2. Fever (> 37.5ºC axillary) or history of fever in the previous 24 hours.
3. Absence of any history of serious side effects to study medications, including allergy to sulphonamide drugs
4. No evidence of a concomitant febrile illness which could interfere with the assessment of clinical treatment outcome
5. Provision of informed consent and ability to participate in 28-day follow-up (patient has easy access to health unit).
6. No history of treatment with an antifolate (sulfadoxine-pyrimethamine [single dose], metakelfin [single dose], TMP/Sulfa [> 3 days]) or amodiaquine (> 2 doses) during the last week (taking final dose within the 7 days prior to study enrolment).
7. Absence of pregnancy (menstruating women who have not missed their last menstrual period).
8. No danger signs or evidence of severe malaria defined as:

- Unarousable coma (if after convulsion, > 30 min)
- Repeated convulsions (> 2 within 24 h)
- Recent convulsions (1-2 within 24 h)
- Altered consciousness (confusion, delirium, psychosis, coma)
- Lethargy
- Unable to drink or breast feed
- Vomiting everything
- Unable to stand/sit due to weakness
- Severe anemia (Hb < 5.0 g/dL)
- Respiratory distress (laboured breathing at rest)
- Jaundice (yellow coloring of eyes)

Prior to the Day 1 return visit, the study laboratory technicians shall assess the results of the Giemsa-stained thick and thin blood smears. These shall not be available until after the patients have been treated and discharged from the clinic. Additional patients will be excluded from the study on Day 1 if they fail to meet the following additional inclusion criteria.

1. *P. falciparum* mono-infection
2. Parasite density > 2000/ul and < 200,000/ul.

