### 6.0 BASELINE EVALUATION AND TREATMENT ASSIGNMENT

### 6.1. Baseline evaluation and procedures:

On Day 0, patients enrolled and assigned study numbers will undergo a complete history and physical examination (Appendix 5 and 6). On day 0, a finger-prick blood sample will be obtained for repeat thick blood smear, thin blood smear, haemoglobin measurement and to save on filter paper for future molecular testing. Because only rapid Giemsa-stained thick smears are typically assessed in the outpatient laboratory, a thick and thin blood smear obtained at enrolment will be stained with 2% Giemsa and read by experienced laboratory technicians who are not involved in direct patient care. Parasite densities will be calculated by counting the number of asexual parasites per 200 leukocytes (or per 500, if the count is <10 parasites/200 leukocytes), assuming a leukocyte count of 8,000/l. A blood smear will be considered negative when the examination of 100 high power fields does not reveal asexual parasites. Gametocytemia will also be determined from thick smears. Thin smears will be used for parasite species identification.

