### 8.2. Analytical plan:

Data analysis will be primarily performed by the project statistician using EPI INFO, SPSS ACCESS and STATA statistical software packages, with additional assistance from members of the UCSF Epi-Center in San Francisco and the University of California, Berkeley, Department of Epidemiology. Primary analyses will be conducted based on intention-to-treat and the primary analysis population will include all randomised subjects fulfilling selection criteria.

Descriptive statistics will be used to summarise baseline characteristics of study patients. Parasite density values will be normalised using logarithmic transformation. All dichotomous variables will be compared between treatment groups using chi-square tests or Fisher’s exact tests. Continuous variables will be compared using t-tests. A p-value of < 0.05 will be considered significant.

Because age is a strong effect modifier in malaria, an age-stratified subgroup analysis for efficacy outcomes is planned. Study subjects will be stratified by age (< 5 years and > 5 years) for analysis of treatment outcome including clinical outcome at 14 and 28 days, and parasitological outcome at 14 and 28 days. Results for the two age groups will be presented independently. After calculating an estimate of association for each of the two age groups, a single adjusted measure of risk difference will be calculated. Other factors that may impact on antimalarial treatment outcome include temperature4 and mean parasite density at presentation ([name], unpublished data). Because a randomised trial is planned, we anticipate that known and unknown confounding factors will be equally balanced between the treatment groups. If by chance, there is an imbalance between the treatment groups for one or more potential confounding variables, adjustment will be made using multiple logistic regression.

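### Day 2 and Day 3 smear positivity is tested crudely and adjusted for Day 0 parasite density only if an imbalance is seen, which gives up precision whenever the arms are balanced

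*Protocol*

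**What the plan says.** Section 4.2.2, item 5, defines the outcome: "Rate of parasite clearance: proportion of positive vs. negative thick blood smears on day 2 and day 3". It is binary and is read on two days.

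Section 8.2 sets the test: "All dichotomous variables will be compared between treatment groups using chi-square tests or Fisher’s exact tests". The same section lists "mean parasite density at presentation" among factors that may bear on treatment outcome, and puts density on a log scale. Its adjustment rule is conditional: "If by chance, there is an imbalance between the treatment groups for one or more potential confounding variables", then "adjustment will be made using multiple logistic regression". The one adjusted estimate planned unconditionally in 8.2 is a risk difference adjusted for age.

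Section 5.2 limits entry to "Parasite density > 2000/ul and < 200,000/ul". Section 6.1 says how the Day 0 value is obtained: "Parasite densities will be calculated by counting the number of asexual parasites per 200 leukocytes" (per 500 when the count is low). It separately defines a negative smear as no asexual parasites in 100 high-power fields.

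Section 8.1 powers 28-day clinical failure only. It gives no smear-positivity rates and no power for clearance.

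**The concern.** The outcome and the baseline are the same quantity, asexual parasites on a thick smear, read on different days. To fall below any fixed detection level, a patient entering at 200,000/ul needs a reduction 100 times larger than one entering at 2,000/ul. Density at entry is therefore expected to influence who is still positive on Days 2 and 3, and 8.2 itself treats it as potentially prognostic.

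An imbalance trigger answers a worry about confounding, not about precision. In the usual case the randomised arms are balanced on density, the trigger does not fire, and variation due to entry density stays in the comparison as noise. A real difference in clearance between regimens is then somewhat more likely to be missed. The trigger also means that the model for this outcome is chosen after the baseline data have been seen.

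**Working it through.** **1. The plan's own figures.** These concern 28-day failure and serve only to fix a realistic number per arm. The formula is the two-sided two-proportion formula with α = 0.05 and 80% power, then the Fleiss continuity correction:

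n = [1.96√(2p̄q̄) + 0.842√(p1q1 + p2q2)]² / (p1 − p2)², corrected n = (n/4)[1 + √(1 + 4/(n|p1 − p2|))]².

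- 15% v 5%: 141 uncorrected, 160 corrected (stated 160).
- 10% v 2%: 138 uncorrected, 162 corrected (stated 162).
- With 10% loss: 160/0.9 = 178 and 162/0.9 = 180 (stated 180 for both).

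The figures reproduce.

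**2. Entry range.** 200,000/2,000 = 100, or 2 log10 units (3.30 to 5.30).

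**3. Power with and without density.** Inputs from the protocol: the density limits, two-sided α = 0.05, and 162 per arm. Assumed inputs, because the protocol gives none:
- Smear positivity of 50% v 35%, or 25% v 13%.
- log10 density uniform over the entry range, or normal centred at 20,000/ul with SD 0.5 and truncated to that range.
- An odds ratio (OR) of a positive smear per 10-fold density of 1, 3, 10 or 30.

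Each setting had 2,000 simulated trials. The uncorrected chi-square test was compared with the likelihood-ratio test for treatment in a logistic model containing log10 density. Entries are power, crude → adjusted, in %.

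| OR per 10-fold | Uniform, 50 v 35 | Uniform, 25 v 13 | Normal, 50 v 35 | Normal, 25 v 13 | Gain (points) |
|---|---|---|---|---|---|
| 1 | 78.2 → 78.6 | 78.8 → 79.2 | 79.8 → 80.0 | 78.8 → 78.9 | about 0 |
| 3 | 78.7 → 83.1 | 79.8 → 82.6 | 78.4 → 81.4 | 80.0 → 81.7 | 2–4 |
| 10 | 77.9 → 88.9 | 81.1 → 88.5 | 78.8 → 86.0 | 79.5 → 85.1 | 6–11 |
| 30 | 77.8 → 96.1 | 76.5 → 90.2 | 78.6 → 91.1 | 79.9 → 89.2 | 9–18 |

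With no treatment difference (25% v 25%), both tests rejected in 4–6% of trials, so both are valid.

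**4. Which odds ratio is plausible?** Suppose a smear is positive when log10 entry density minus a log10 reduction exceeds a fixed level, and the reduction is independent of entry density with between-patient standard deviation SD. Then OR ≈ exp(1.7/SD):

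- SD 0.6: 17
- SD 1.0: 5.5
- SD 1.5: 3.1
- SD 2.0: 2.3

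Simulating this model directly with 160 per arm gave gains of about 3.5 to 19.5 points for SD 0.6 to 1.0, 1 to 3 points for SD 1.5, and 0.5 to 2.5 points for SD 2.0. The detection level was set at 8,000/500 = 16/ul, one parasite per 500 leukocytes. That only approximates the protocol's 100-field rule. The protocol does not give SD.

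**The case against.** The best reply is that 8.2 already names this covariate and this model. It does, so a reader who infers that the plan ignores Day 0 density altogether goes too far. The dispute is only whether adjustment should wait for an observed imbalance. On that the objection does not succeed: the clause does nothing for precision when the arms are balanced.

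A reader might also infer from the 100-fold range that entry density largely determines who is still positive. The documents do not support that. Section 8.2 says only that density may matter, and says nothing specific to Day 2 or Day 3 smears. If patients differ widely in how fast they clear parasites, the gain falls to a point or two.

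Third, no power is lost against a target. The 80% in 8.1 belongs to 28-day clinical failure, and item 5 is one of seven secondary efficacy outcomes. This stands, as does the validity of the crude test under randomisation.

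Last, covariates for a secondary outcome are often left to the statistical analysis plan. That would answer a complaint that something is missing. Here the protocol fixes both the crude default and the imbalance trigger, so the objection has force against the weight of the point but not against making it.

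**Conclusion.** The point holds as a minor matter of efficiency. For Day 2 and Day 3 smear positivity, 8.2 makes the crude comparison the default and lets an observed imbalance decide whether a baseline value already in hand is used. Nothing is biased and no type I error is inflated by the crude test.

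The supportable gain from adjusting regardless runs from negligible to roughly 20 power points, depending almost wholly on how strongly density predicts later positivity, which the documents do not quantify. The calculations assume the positivity rates, the density distributions and a logistic or threshold relation. They compare always adjusting with never adjusting. The adjust-on-imbalance rule was not simulated, nor were the age covariate and the standardised risk difference proposed below.

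**What to change.** In 8.2, state that smear positivity on Day 2 and on Day 3 will each be compared by logistic regression with treatment, log10 Day 0 parasite density and the randomised age stratum (under 5 years; 5 years and above) as covariates, whatever balance is observed. Report the treatment effect as a risk difference standardised over the baseline covariates, because the odds ratio from an adjusted model does not answer the same question as the crude one. Keep the crude proportions as description. Exempt this outcome from the imbalance clause, and name in advance what is done if an arm has no positive smears, where the logistic treatment estimate is not finite. The Fisher test already in 8.2 could serve.

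The cost is a few lines of text and slightly more analysis work. Day 0 density is already on the case record form (item 44), the log transformation is already planned, and age is already a randomisation stratum.

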### FOLLOW-UP EVALUATION AND PROCEDURES

7.1. Follow-up schedule:

Patients will go home on Day 0 and will be asked to return to the clinic for follow-up on Days 1, 2, 3, 7, 14, 21, 28, and any unscheduled day that they feel ill. All patients will be reimbursed the cost of their transport to and from the clinic. Details about the location of the patient’s residence will be obtained and if a subject does not return for a scheduled clinic follow-up appointment, the study personnel shall visit them at home. Patients who return on Day 1 and fail to fulfil the criteria of *P. falciparum* mono-infection with a parasite density of > 2000 parasites/ul and < 200,000 parasites/ul will be excluded from further study and referred to OPD for management. At each repeat visit, temperature will be measured and a focused physical examination will be performed. A finger prick blood sample will be obtained on Days 2, 3, 7,14, 21 and 28 (and any extra day) to repeat thick blood smears and to save on filter paper. Haemoglobin will be re-evaluated either on day 28 or at the time of clinical treatment failure. All thick smears will be assessed for parasite density and presence of gametocytes. Any patient who is suspected of clinical treatment failure after Day 3 will have a repeat thick and thin smear obtained.

Follow-up Schedule

|  | **Day 0** | **Day 1** | **Day 2** | **Day 3** | **Day 7** | **Day 14** | **Day 21** | **Day 28** | **Extra Day** | **When necessary** |
| --- | --- | --- | --- | --- | --- | --- | --- | --- | --- | --- |
| Study medications | X | X | X |  |  |  |  |  |  |  |
| History | X | X | X | X | X | X | X | X | X |  |
| Temperature measurement | X | X | X | X | X | X | X | X | X |  |
| Physical exam | X | X | X | X | X | X | X | X | X |  |
| Neurologic exam (3-arm study only) | X |  |  |  | X | X | X | X | * |  |
| Thick blood smear | X |  | X | X | X | X | X | X | X |  |
| Thin blood smear | X |  |  |  |  |  |  |  |  | CTF after day 3 |
| Filter paper sample | X |  |  | X | X | X | X | X | * |  |
| Haemoglobin | X |  |  |  |  |  |  | X | * | If CTF, on day of failure |
| Assessment for adverse drug event | X | X | X | X | X | X | X | X | X |  |

X = perform this task

* As indicated

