### 7.3. Management of clinical treatment failures:

Patients who are classified as clinical failures (early or late treatment failure, Appendix 3) will be treated with quinine 10 mg/kg orally three times a day for 7 days. Any patient who develops evidence of severe malaria or danger signs during malaria follow-up, will be referred for appropriate treatment with parenteral quinine at the local facility or hospital. Any patient who responds clinically to treatment, but has a positive thick blood smear on day 28 (asymptomatic parasitaemia) will be treated with standard doses of oral quinine. Hemoglobin will be repeated on the day the patient is classified as a clinical treatment failure.

- 1. **Exclusion after enrolment and loss to follow-up:**

Patients will be excluded from the study after enrolment if any of the following occurs:

- 1. Use of antimalarial drugs outside of the study protocol.
  2. Development of concomitant febrile illness that may interfere with outcome classification.
  3. Withdrawal of informed consent.

Patients who fail to attend a follow-up visit and are unable to be located within 24 hours on Days 1-3 or within 48 hours on Days 4-28 will be considered lost to follow-up.

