### 8.0 STATISTICAL CONSIDERATIONS

### 8.1. Sample size calculations:

The sample size calculations will be made for each study based on the estimated efficacy of the combination regimens to be studied in the given region. For the purposes of sample size calculation, the risk of clinical failure at 28 days will be the main outcome. If the null hypothesis states that there is no difference in clinical outcome between the treatment groups, we plan to test the alternative hypothesis that treatment with an alternative combination regimen (AQ/SP or AS/AQ) will decrease the likelihood of clinical failure at 28 days of follow-up. Calculations will be made using an α = 0.05 and a statistical power of 80% based on a two-sided test. Allowance will be made for a possible 10% loss to follow-up to ensure that an adequate number of patients complete the study. Based on this, the sample size for the various drug combinations is summarized below:

Sample size for the different drug combinations

| **Presumed level of resistance.** | Resistance to CQ/SP | Resistance to AQ/SP or AS/AQ | Number per group | Number per group adjusted for loss to follow up. |
| --- | --- | --- | --- | --- |
| High resistance community (urban areas) | 15% | 5% | 160 | 180 |
| Low resistance community (rural areas) | 10% | 2% | 162 | 180 |

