### APPENDIX 3. OUTCOME CLASSIFICATION

### Clinical Outcome Classification System

| ACR (Adequate Clinical Response)   - Absence of parasitemia on Day 28, without previously meeting criteria for ETF or LTF - Temperature < 37.5C (Axillary) and no history of fever in last 24 hours on day 28 irrespective of the presence of parasitemia, without previously meeting any of the criteria of ETF or LTF |
| --- |
| ETF (Early Treatment Failure): Days 0, 1, 2, and 3  - Development of danger signs or severe malaria on Days 0-3 in the presence of parasitemia - Parasitemia on Day 2 higher than Day 0 count irrespective of temperature - Temperature > 37.5C (Axillary) on Day 3 in presence of parasitemia - Parasitemia on Day 3 > 25% Day 0 count |
| LTF (Late Treatment Failure): Days 4 To 28  - Development of danger signs or severe malaria on Days 4 to 28 in the presence of parasitemia, without previously meeting any of the criteria of ETF. - Temperature > 37.5C (Axillary) or history of fever in last 24 hours on Days 4 to 28 in the presence of parasitemia, without previously meeting any of the criteria of ETF. |

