4. **AEs in patients classified as treatment failures** – Formal study follow-up ends when a patient is classified as a treatment failure (ETF or LTF), and patients should be treated with quinine and managed according to good medical practice. Additional follow-up for AEs in patients classified as treatment failures, is not typically indicated, unless the AE is serious, or is felt to be probably or definitely related to the study medications. The Kampala core facility staff should be contacted with any questions about follow-up of AEs in patients with treatment failure.

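### The Day 0 to Day 28 haemoglobin outcome has no Day 28 value for patients who fail clinically before Day 28, so read literally it compares only patients who had not failed, a group expected to differ between arms.

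*Protocol*

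**What the plan says.** Section 4.2.2 lists seven secondary efficacy comparisons between treatment groups. The sixth is "Change in mean haemoglobin from day 0 to 28".

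The measurement schedule is in section 7.1: "Haemoglobin will be re-evaluated either on day 28 or at the time of clinical treatment failure". The schedule table there has a haemoglobin mark on Day 28 and adds, for clinical treatment failures, "If CTF, on day of failure". Section 7.3 agrees: "Hemoglobin will be repeated on the day the patient is classified as a clinical treatment failure".

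Appendix 10, in its part on the length of adverse event follow-up, states: "Formal study follow-up ends when a patient is classified as a treatment failure (ETF or LTF"). Follow-up beyond that point is described only for certain adverse events.

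Appendix 3 places early failure on Days 0 to 3 and late failure as "LTF (Late Treatment Failure): Days 4 To 28".

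On analysis, section 8.2 says "Continuous variables will be compared using t-tests". It gives no separate rule for haemoglobin.

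**The concern.** The outcome is tied to Day 28, while the schedule gives each patient one planned follow-up haemoglobin, whose day depends on whether and when the patient fails. For anyone failing before Day 28, the quantity named in item 6 is not planned to be observed.

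An analyst who follows the wording must therefore leave these patients out. The comparison is then between the patients in each arm who had not failed. Membership of that group is decided after randomisation by the same event that forms the primary outcome, and the trial is designed on the expectation that this event is less frequent under the alternative regimens. The two sets of remaining patients are no longer protected by randomisation. Any difference in haemoglobin that arises because one regimen has fewer failures is removed from view.

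The alternative is to treat the failure-day value as if it were a Day 28 value. That keeps the patients, but puts measurements from as early as the first days of follow-up together with Day 28 measurements, in shares that again differ by arm.

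**Working it through.** **1. Is a Day 28 value planned for a clinical failure?**

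| Patient | Planned follow-up haemoglobin | Usable for item 6 as worded? |
|---|---|---|
| Does not fail | Day 28 | Yes |
| Fails on Day 28 | Day 28, which is the failure day | Yes |
| Fails before Day 28 | Failure day; formal follow-up then ends | No |

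The gap concerns the third row only.

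**2. Reproducing the plan's figures.** Section 8.1 gives failure risks of 15% v 5% ("High resistance community (urban areas) | 15% | 5% | 160 | 180") and, for low resistance, 10% v 2% with 162 per group, 180 after loss. It uses two-sided α = 0.05 and 80% power. The standard two-proportion formula is

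n = [1.96 √(2p̄(1−p̄)) + 0.8416 √(p1(1−p1) + p2(1−p2))]² / (p1−p2)².

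- Without continuity correction it gives 141 and 138.
- With continuity correction it gives 160 and 162, which match the stated figures.
- Dividing by 0.90 for loss gives 178 and 180, against the stated 180 for both.

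The rates and group sizes are therefore sound as inputs. No figure is stated for haemoglobin.

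**3. Patients affected per group** (n × failure risk, before loss to follow-up):

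| Setting | n | CQ/SP failures | Alternative failures | Left with a Day 28 value |
|---|---|---|---|---|
| 15% v 5% | 160 | 24 | 8 | 136 v 152 |
| 10% v 2% | 162 | 16.2 | 3.2 | 145.8 v 158.8 |

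With 180 per group the failures are 27 v 9 and 18 v 3.6. The ratio is 0.15/0.05 = 3 or 0.10/0.02 = 5. Failures that fall on Day 28 itself lower the counts slightly.

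**4. Effect on the arm contrast.** Let R be the mean change in patients who do not fail, and let failures gain h less, with h taken as equal in both arms. The mean change over all patients in an arm is R − p·h. Then

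all-patient contrast = (R2 − R1) + (p1 − p2)·h,

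while the contrast without failures is R2 − R1. Leaving failures out shifts the result by (p1 − p2)·h. The protocol gives no haemoglobin change, so h is an assumption, shown over a range:

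| h (g/dL, assumed) | 15% v 5%: 0.10 × h | 10% v 2%: 0.08 × h |
|---|---|---|
| 0.5 | 0.05 | 0.04 |
| 1.0 | 0.10 | 0.08 |
| 1.5 | 0.15 | 0.12 |
| 2.0 | 0.20 | 0.16 |

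Pooling failure-day values as though taken on Day 28 gives a shift of the same form. The gap is then that between a failure's change on the failure day and the change the same patient would have shown on Day 28.

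**The case against.** The strongest reply is that item 6 is a one-line label for a secondary outcome. The schedule deliberately collects a haemoglobin at failure, so the natural reading is that this value stands in when follow-up ends early, and a statistical analysis plan that is not shown here could say so. Part of this stands: a second value is planned for every clinical failure, and the choice of how to use it could be written elsewhere. But the protocol itself fixes the end point at Day 28 and fixes a schedule that cannot supply it for earlier failures. An analysis plan can depart from that wording; it cannot recover a value that was never collected.

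A second objection is that using failure-day values leaves the timing mismatch in place. This stands fully. Measurement day is set by failure, and adjusting for Day 0 haemoglobin does not change that.

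Three stronger readings are tempting but not supported:

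- *That no clinical failure has a Day 28 value.* A patient failing on Day 28 does.
- *That the plan hides a main expected benefit.* The protocol states no haemoglobin hypothesis and sizes the trial on clinical failure alone.
- *That a Day 0 mean over everyone will be set against a Day 28 mean over responders.* The phrase about change in mean permits this, but section 8.2 names only t-tests, which fit within-patient changes equally well.

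**Conclusion.** The inconsistency is real and confined to one secondary outcome. The primary outcome and the sample size are untouched. Followed literally, item 6 conditions on not failing before Day 28, and the design rates imply three to five times as many exclusions in CQ/SP as in the alternative arm. Those rates are planning assumptions, not results.

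A reader might infer a known bias in a known direction, or express it in standard errors. The protocol supports neither: it gives no haemoglobin change or standard deviation, and nothing on what failures' haemoglobin would have been on Day 28 after rescue treatment. The shifts of 0.05 to 0.20 g/dL and 0.04 to 0.16 g/dL are illustrations. They rest on an assumed gap of 0.5 to 2.0 g/dL that is equal in both arms, and their sign depends on failures gaining less.

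**What to change.** Reconcile section 4.2.2 item 6 with sections 7.1 and 7.3 and Appendix 10, as follows:

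1. Define item 6 as the within-patient change in haemoglobin from Day 0 to the last scheduled measurement (Day 28, or the day of clinical failure), in all patients with a second value.
2. In place of the plain t-test, compare arms with a linear model containing Day 0 haemoglobin and the age stratum used for randomisation in section 4.3.
3. Report the day of measurement by arm.
4. Show the Day 28 change in patients who did not fail earlier as supportive, labelled as conditional on not failing.

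The cost is a change of wording and a simple model; the failure-day haemoglobin is already scheduled. The downside should be stated with the result: measurement time still differs by arm because failure sets it. The estimate is therefore a change up to failure or Day 28, and not a pure Day 28 effect. The latter would need Day 28 haemoglobin to be sought in failures too, which the present schedule does not provide.
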